### Trial design and setting

This study is a randomized, double-blinded, parallel group, placebo-controlled trial. Eligible participants will be randomly assigned to the experimental group (Guizhi-Shaoyao-Zhimu decoction) or the control group with a 1:1 ratio. The subjects will be selected from patients with early active rheumatoid arthritis who visited the Rheumatology Department of Shuguang Hospital affiliated with Shanghai University of Traditional Chinese Medicine. We plan to recruit patients from participating hospitals via poster, networking, or WeChat. The posters will be placed on bulletin boards or other assigned places in the hospitals. At least one staff member (a postgraduate or doctor) will specialize in patient recruitment. Their contact information and clinic for screening visit will be detailed described in the recruitment advertisement. The design of the study follows a strict scientific clinical research methodology and complies with the principles outlined in the Declaration of Helsinki and the guidelines for good clinical practice. At any stage of the clinical study, a participant can withdraw from the clinical research without discrimination or retaliation. Patient rights and interests are not affected. If harm or injury related to the clinical research occurs, then the subjects can be appropriately compensated. The clinical study can be conducted only after the signature of the subject or legal representative/guardian is received with the date specified. If the subject or legal representative/guardian cannot read, a witness should be present. After a detailed explanation of the informed consent form, the subject or legal representative/guardian can provide consent, and the witness can sign and date the form. The flow chart and trial schedule are shown in Fig. 1 and Table 1, respectively.

**Fig. 1 Fig1:**
[figure not shown]
Study flow chart

**Table 1 Tab1:** Schedule of study procedures

		Study period					
	Enrolment	Allocation	Post-allocation (days)				Close-out ***90d+***
**Time point**	***- -T0d***	***-T0d***	***T0d***	***T30d***	***T60d***	***T90d***	
**Enrolment**							
Patients with early RA	X						
RF	X						
Diagnosis and investigation of the distribution of TCM syndrome types	X						
**Informed consent**	X						
General information	X						
General physical examination	X						
**Allocation**		X					
**Interventions**							
Western medicine as well as TCM placebo combined group			X	X	X	X	
Western medicine as well as TCM combined group			X	X	X	X	
**Assessments**							
Blood routine			X	X	X	X	
Urine routines			X			X	
Hepatic and renal function (ALT, AST, AKP, eGFR, Scr, BUN)			X	X	X	X	
TCM symptoms			X	X	X	X	
ESR, CRP			X	X	X	X	
DAS28, VAS			X	X	X	X	
US7			X			X	
sCD14, MMP3, TIMP1			X			X	
Adverse events			X	X	X	X	

A total of 152 participants will be randomized into the control group or the experimental group. Assessors blinded to the randomization will collect data during the intervention period at baseline and at study months 1, 2, and 3. The peripheral blood levels of matrix metalloproteinase 3 (MMP3), matrix metalloprotease 1 (TIMP1), and soluble cluster of differentiation 14 (sCD14) will be detected before and after treatment to explore the biochemical mechanisms of Guizhi-Shaoyao-Zhimu decoction for the treatment of active RA

### Eligibility criteria

To participate in the trial, potential participants must fulfill all the following criteria:

#### Diagnostic criteria

Diagnostic criteria for RA: According to the criteria for the classification of RA proposed by the American College Rheumatology (ACR) and European League against Rheumatism (EUHLAR) in 2010, participants with a score of 6 or above who were diagnosed with RA [10].Diagnostic criteria for active RA: Disease Activity Score (DAS28) > 2.6. DAS28, the most commonly used comprehensive score in RA, is used to evaluate the disease activity of RA patients with scores ranging from 0 to 10 [11]. According to EULAR diagnostic criteria for RA activity, DAS28 > 2.6. This project aims to study active RA patients, so the participants in this study should have a DAS28 score greater than 2.6.Diagnostic criteria for TCM syndrome differentiation: according to the Guidelines for Clinical Research of Chinese Medicine (New Drug) [12], the participants had to present with at least two of the primary symptoms and more than two of the secondary symptoms listed in the following to be diagnosed with wind dampness heat bi syndrome.
Primary signs and symptoms:
IRedness and swelling of jointsIIAcute joint painIIIStiff joints in the morningIVActivity limitationSecondary symptoms:
IAversion to cold with feverIIThirsty upsetIIIDry stools and yellow urineIVRed tongue with yellow or dry furVRapid and slippery pulse

#### Inclusion criteria

Patients who meet the following criteria will be deemed eligible for the trial:
Meet the diagnostic criteria for RA, meet the diagnostic criteria for active RA, and meet the wind dampness heat bi syndromeAged 18–80 years with a disease course of less than 1 yearDisease Activity Score in 28 joints-Erythrocyte Sedimentation Rate (DAS28-ESR) ≥ 2.6 (rounded to 1 decimal place)Patients receiving NSAIDs and hormone therapy were given a stable dose for at least 30 days before entering the trial and remained at the same dose for the rest of the treatment.Treatment with other DMARDs must be interrupted for at least 30 days before entering the trial.

#### Exclusion criteria

Patients who meet the following criteria will be excluded from the trial:
Patients with interstitial lung disease accompanied by severe elevations of liver enzymesWomen who are pregnant, breastfeeding, or who have recently prepared for childbirthPersons who are allergic or sensitized to the test drugsPatients with severe primary diseases of the heart, liver, kidneys, brain, endocrine system and hematopoietic system, psychiatric disorders, etc.The presence of other rheumatic diseases such as systemic lupus erythematosus, Sjogren’s syndrome, and myositis.

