**Methods:**

This study is a randomized, double-blinded, parallel group, placebo-controlled trial. A total of 152 adult participants with early RA will be enrolled, with balanced treatment allocation (1:1). The experimental intervention will be Guizhi-Shaoyao-Zhimu decoction plus the conventional medicine methotrexate and the control intervention will be placebo plus the conventional drug methotrexate for 3 months. In addition, both groups will receive folic acid during treatment to prevent side effects from methotrexate. The primary outcomes are the erythrocyte sedimentation rate (ESR), C-reactive protein (CRP), hepatic and renal function, visual analog scale, disease activity score in 28 joints, measurement scale for TCM symptoms, and 7-joint ultrasound score.

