#### Medication method

For the experimental group (Western medicine + Guizhi-Shaoyao-Zhimu decoction), Guizhi-Shaoyao-Zhimu decoction will be taken twice a day (30 g each time). Combined MTX will be taken orally once a week (10~15 mg). Folic acid tablets will be taken orally twice a week (5 mg).

For the control group (Western medicine + TCM placebo), TCM placebo twice a day, 30 g each time. MTX is taken orally 10~15 mg once a week. Folic acid tablets should be taken 5 mg orally twice a week.

Each patient lasted for 3 months.

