### Measurement items and time points of data collection

#### Outcome measure

##### General information (before treatment)

The patients’ general information, including demographic data, general medical examination items, and general clinical data will be collected at baseline.
Demographic data: The patients’ name, sex, age, nationality, occupation ID number, date of birth, home address, and contact information will be collected.General medical examination items will include respiration, body temperature, pulse, blood pressure, tongue coating, and pulse measurements.General clinical data will include history of present illness, past medical history, family history, personal life history, menstrual history, marital history, allergy history, and social history.

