### Safety guarantee and evaluation

All trial interventions will be conducted under the guidance of rheumatology experts. The researchers will closely observe the physical conditions of the participants. Routine hematuria and liver and kidney function tests will be performed before enrollment and at 1, 2, and 3 months after enrollment. Adverse events and serious adverse events will be recorded by all participants and will be reported to the principal investigator and professional leader in the event of adverse events to find a reasonable solution. Conduct monthly internal team review of adverse events related to drug use. In addition, the safety and efficacy of the intervention will be examined by two clinicians and statisticians independent of the trial, who will also make professional recommendations on the pace of trial recruitment, whether to continue and terminate the trial, and, if necessary, on amendments to the protocol. Subjects have the right to withdraw their consent to participate in the study at any time for any reason, without any consequences for further treatment.

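### The lung and liver exclusion requires both conditions together, so a patient with only one of them can be enrolled to weekly methotrexate

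*Protocol article*

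**What the plan says.** The Exclusion criteria section has five items. The first excludes patients with "interstitial lung disease accompanied by severe elevations of liver" enzymes. The fourth excludes "severe primary diseases of the heart, liver, kidneys, brain, endocrine system and hematopoietic system, psychiatric disorders, etc". The other three concern pregnancy and breastfeeding, allergy to the test drugs, and other rheumatic diseases.

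Under Medication method, the experimental arm is told: "Combined MTX will be taken orally once a week (10~15 mg"), and for the control arm: "MTX is taken orally 10~15 mg once a week". Treatment lasts 3 months. The Abstract adds that "both groups will receive folic acid during treatment to prevent side effects from methotrexate".

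On testing, Safety guarantee and evaluation states that "liver and kidney function tests will be performed before enrollment and at 1, 2, and 3 months after enrollment". Table 1 lists "Hepatic and renal function (ALT, AST, AKP, eGFR, Scr, BUN") with its first tick at T0d, in the column after allocation. Medical history is taken before treatment: "General clinical data will include history of present illness, past medical history". Table 1 ticks general information and the general physical examination at enrolment.

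**The concern.** The first exclusion joins two conditions with wording that means both must be present. A patient with interstitial lung disease and normal enzymes does not meet it. Nor does a patient with severely raised enzymes and no lung disease. The protocol treats these two conditions as reasons to keep someone out of the trial, yet as written it reliably keeps out only those who have both.

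The issue is patient safety at entry. Every participant in either arm takes methotrexate weekly, and the protocol acknowledges side effects of that drug by giving folic acid against them. Because the rule applies equally to both arms and acts before randomisation, it does not bias the treatment comparison.

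**Working it through.** The plan gives no figure to reproduce here. The check is whether any other rule covers each condition on its own, followed by a short exposure calculation.

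**Other rules that might cover the gap**

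- *Diagnostic and inclusion criteria.* They cover RA classification, disease activity, TCM syndrome, age, disease duration and prior medication. None mentions the lung or liver enzymes.
- *Severe primary disease item.* It names heart, liver, kidneys, brain, endocrine and hematopoietic systems and psychiatric disorders, then ends in 'etc.'. The lung is not named. Raised enzymes count only when they amount to severe primary liver disease.
- *Other rheumatic diseases item.* It gives lupus, Sjogren's syndrome and myositis as examples, and addresses neither condition.
- *Drop out criteria.* One ground is breach of a key eligibility criterion. A patient with lung disease alone breaches no named criterion, so it is not triggered. The serious adverse reaction ground acts only after harm.
- *Safety guarantee and evaluation.* Liver tests are promised before enrolment, but no eligibility rule is attached to the result. The scheduled laboratory tests include liver and kidney panels and nothing specific to the lung.

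**Coverage, read literally**

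| Interstitial lung disease | Severely raised enzymes | Excluded? |
|---|---|---|
| Yes | Yes | Yes, by the first item |
| Yes | No | By no named criterion; at most through 'etc.' |
| No | Yes | Only if it reflects severe primary liver disease |

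Of three combinations with at least one condition, one is fully excluded, one partly, and one not by any named criterion.

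**Scheduled methotrexate exposure of a patient so admitted**

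- Inputs: 10 to 15 mg once a week (Medication method); last treatment time point T90d (Table 1).
- Doses: 90 / 7 = 12.9, about 13.
- Total: 13 × 10 mg = 130 mg to 13 × 15 mg = 195 mg.

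Every participant is scheduled for this amount. It describes what an inappropriately admitted patient would receive and does not estimate excess risk.

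**The case against.** The strongest reply is that this is a slip of language. The intended meaning was probably 'or', the article's English is uneven elsewhere, and a full protocol may word it correctly. Interventions are supervised by rheumatology experts, who take a history, examine the patient and see liver tests, and would be unlikely to enrol someone with evident lung disease or very high enzymes. The 'etc.' gives them a basis to refuse. Nor do the documents state that methotrexate harms the lung, so the danger for that half is not shown from the text.

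Part of this stands. A slip is the likeliest explanation, careful clinicians would often avoid the consequence, and the number of patients affected is unknown. But the criterion is stated in full and grammatically, nothing in the document corrects it, and an entry rule should not depend on each investigator guessing its intent. Nor does the point need an outside source on methotrexate: the protocol itself chose both conditions as grounds for exclusion, and the wording fails to carry that out. Monitoring and withdrawal limit the consequence after entry without changing who is let in.

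Two practical objections also hold. The word 'severe' has no threshold, so the enzyme criterion would still involve judgement after the line is split. And relying on history finds only interstitial lung disease that is already known.

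**Conclusion.** The concern holds and should be fixed. Read literally, the exclusion admits patients with interstitial lung disease alone, unless an investigator invokes 'etc.', and patients with severely raised enzymes alone, unless these reflect severe primary liver disease. Each would be scheduled for about 13 weekly methotrexate doses, 130 to 195 mg in total.

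This rests on the ordinary meaning of the wording and on the article reflecting the operative criteria. How often it would happen cannot be estimated from the documents. No effect on the treatment estimate, the power or the type I error is claimed.

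**What to change.** Replace the first exclusion item with two separate ones:

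1. Interstitial lung disease.
2. Severe elevation of liver enzymes.

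Apply the first from the medical history already collected at baseline. Apply the second to the liver test that the safety section promises before enrolment, and state that the result must be reviewed before randomisation. Table 1 should agree, with the hepatic panel ticked in the enrolment column; at present its first tick is at T0d. The investigators could also say what they mean by severe; the documents offer no basis for proposing a value here.

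One line becomes two. No new test is needed, given the pre-enrolment test already promised; if sites have been following Table 1 instead, the first liver panel moves ahead of allocation. The downside is a few more screen failures.

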#### The drop out criteria

Patients will be terminated or withdrawn from the trial if they encounter any of the following conditions:
Violation of any of the key inclusion or exclusion criteriaFailure to take prescribed drugs during the trial, affecting the efficacy evaluationTaking other TCM that are prohibited by this protocol, so that the efficacy and safety of the treatment cannot be correctly judgedSerious adverse reactions to the experimental or control drugsThe desire to withdraw from the experimentLoss to follow-up, death, or withdrawal from the trial due to any other reason

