### Sample size calculation

To determine the sample size, we inquired about the previous research contents. The effective rate of methotrexate in the treatment of rheumatoid arthritis was 40% [8], and that of Guizhi-Shaoyao-Zhimu decoction was 64% [9]. If *α* = 0.05 and the test efficacy 1 − *β* = 0.80, then the sample size; thus, *n* = 122, with 61 patients in each treatment group. Considering a 20% dropout rate, the planned sample size for randomization was increased to 152.
$$ {n}_1={n}_2=\frac{{\left[{Z}_{\alpha /2}\sqrt{2p\left(1-p\right)}+{Z}_{\beta}\sqrt{p_1\left(1-{p}_1\right)+{p}_2\left(1-{p}_2\right)}\right]}^2}{{\left({p}_1-{p}_2\right)}^2} $$

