### Statistical analysis

An independent statistician will perform statistical analysis according to the statistical analysis plan using SPSS software (version 26; SPSS Inc., Chicago, IL, USA). Continuous variables will be expressed as the mean (standard deviation) if the data are normally distributed; otherwise, they will be expressed as the median (interquartile). Categorical variables will be presented as frequencies (percentages). Baseline analyses will be performed using analysis of variance or nonparametric tests for continuous variables, and chi-squared or Fisher’s exact tests for categorical variables, respectively. Changes from baseline to post-treatment in DAS28, VAS, TCM syndrome scores, and US7 will be analyzed using analysis of covariance with associated 95% confidence intervals. A two-sided *P* value of 0.05 or less is considered statistically significant. Multiple imputation will be used to handle any missing data.

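### The drop-out rule takes patients out of the trial rather than off study drug, so measurable outcomes, including the only post-baseline US7, are lost and left to imputation

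*Protocol article*

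**What the plan says.** The section on drop-out criteria (Protocol article) opens: "Patients will be terminated or withdrawn from the trial if they encounter any of the following conditions". The list that follows mixes two kinds of event:

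- **Decided by the trial team:** breach of a key eligibility criterion; missed study drug to a degree that compromises the efficacy assessment; use of prohibited TCM that prevents a judgement of the treatment; serious adverse reaction to either study drug.
- **Outside the team's control:** the patient's own wish to leave, loss to follow-up, death and other withdrawal.

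The note to Table 1 says: "Assessors blinded to the randomization will collect data during the intervention period at baseline and at study months 1, 2, and 3". In that table DAS28, VAS and TCM symptoms are marked at T0d, T30d, T60d and T90d, and US7 only at T0d and T90d. (The Outcome variables section gives a single set of times, in weeks, for all primary outcomes, which disagrees with Table 1. The item-by-item schedule in Table 1 is used here.)

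The Statistical analysis section says: "Changes from baseline to post-treatment in DAS28, VAS, TCM syndrome scores, and US7 will be analyzed using analysis of covariance". On gaps in the data it says: "Multiple imputation will be used to handle any missing data". The sample size section expects a sizeable loss: "Considering a 20% dropout rate, the planned sample size for randomization was increased to 152".

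**The concern.** The rule does not separate stopping study drug from leaving the trial. A patient who stops taking granules, takes another herbal product or has a serious reaction may be quite willing to attend at day 90. The patient's wish to leave is a separate item on the list, so the other items remove people who have not asked to go.

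The loss is most serious for US7, which the abstract names among the primary outcomes and which belongs to the first study objective. With no interim scan, a patient withdrawn before T90d contributes only a baseline value. DAS28, VAS and TCM scores keep their T30d and T60d values up to the point of withdrawal.

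Multiple imputation keeps these patients in their assigned arm. In its usual missing-at-random form, it gives them values like those of patients who adhered to and tolerated treatment. (That form is an assumption, since the article does not state one.) Non-adherence and serious reactions pick out the patients for whom this is least credible, and both may differ by arm. If withdrawn patients do worse, more withdrawals for reactions on the decoction would flatter it, while more placebo patients turning to prohibited TCM would work against it.

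A later analysis plan can change the imputation model, but it cannot recover a day-90 visit that never took place.

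**Working it through.** **The plan's own figure.** The dropout step reproduces: 122 / (1 − 0.20) = 152.5, against 152 planned. Of 152 patients, 20% is about 30 who could lack a day-90 value. The article does not say how many of these would be withdrawn by the trial team. (The printed formula gives 66.8 per arm rather than 61. That is a separate matter; 61 serves below only as a yardstick.)

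**Inputs from the article.** Methotrexate response 40%, overall dropout 20%, 61 per arm, two-sided 0.05, power 80%.

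**Assumed inputs.** The split of withdrawal between arms, and how much worse withdrawn patients do. The article gives neither.

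**Response scale.** Suppose there is no true difference: 40% respond in each arm among all randomised, and 20% respond among the withdrawn. With a share *w* withdrawn, response among the retained, which missing-at-random imputation carries over to the withdrawn, is (0.40 − 0.20*w*) / (1 − *w*):

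| *w* | Response in retained |
|---|---|
| 0.10 | 0.4222 |
| 0.15 | 0.4353 |
| 0.20 | 0.4500 |
| 0.25 | 0.4667 |
| 0.30 | 0.4857 |

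Spurious differences:

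- 20% vs 20%: 0
- 25% vs 15%: 0.4667 − 0.4353 = 3.1 percentage points
- 30% vs 10%: 0.4857 − 0.4222 = 6.3 percentage points

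Swapping the arms reverses the sign.

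**Change-score scale (the planned ANCOVA).** If withdrawn patients are *d* SD worse than their imputed values in both arms, the bias is *d* × (*w*₁ − *w*₂), in favour of the arm with more withdrawals:

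| *d* (SD) | 20% vs 20% | 25% vs 15% | 30% vs 10% |
|---|---|---|---|
| 0.25 | 0 | 0.025 | 0.05 |
| 0.5 | 0 | 0.05 | 0.10 |
| 1.0 | 0 | 0.10 | 0.20 |

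Equal withdrawal is no protection if the withdrawn fare differently by arm. At 20% in each arm, a 0.5 SD departure in one arm only gives 0.20 × 0.5 = 0.10 SD in either direction. Opposite departures of 0.5 SD give 0.20 SD.

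**Yardstick.** The detectable effect at 61 per arm is (1.960 + 0.842) × √(2/61) = 0.507 SD. Biases of 0.05 and 0.10 SD are about 10% and 20% of this.

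**Do interim values rescue the imputation?** Not when the worsening follows withdrawal. A simulation used regression imputation with T30d values in the model (76 per arm, 4000 runs, 30% vs 10% withdrawn, 0.5 SD loss after stopping drug). Imputation gave a difference of 0.000 SD and full follow-up gave 0.098 SD. The set-up differs from the response example: here the drug has no effect while taken, and the all-randomised difference arises from stopping. The gap between imputation and the all-randomised result is again about 0.10 SD, as the formula gives.

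**The case against.** The strongest reply is that this reads too much into a condensed article. It never says outright that assessments stop, and early-termination visits are detail that a full protocol often holds. Parts of the list, such as death and loss to follow-up, classify events rather than order a withdrawal. Two of the triggers are narrowed to cases where efficacy cannot be judged. The sentence under Table 1 could be read as covering every randomised patient. These points limit how many patients the rule would remove. They do not change what it says: the object of withdrawal is the trial, and that ordinarily ends assessment.

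A second reply is that calling the gap a bias presumes interest in all randomised patients as assigned, while the objective speaks of patients treated with the decoction. The article does not settle this. But continued assessment still allows an on-treatment analysis, whereas stopping assessment rules out the all-randomised one.

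A third reply is that every magnitude is assumed, and this stands. Only withdrawals decided by the trial team are recoverable. If half of the arm imbalance were of that kind (also an assumption), 0.05 and 0.10 SD become 0.025 and 0.05 SD. Eligibility breaches are mostly fixed at baseline and, under blinding, have little reason to differ by arm. The response example also does not correspond to a planned analysis, since the plan is ANCOVA of changes.

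**Conclusion.** The concern holds as a cheap improvement. The written rule discards day-90 outcomes from patients who could be measured, and for US7 it leaves nothing after baseline. Under the assumptions above, the effect in all randomised patients could be off by 0 to 0.10 SD when the withdrawn are 0.5 SD worse in both arms, and by up to 0.20 SD at 1.0 SD worse or with opposite departures in the two arms. The sign is unknown. The bias is zero if withdrawal and the outcomes of the withdrawn are the same in both arms. The avoidable part is smaller than these figures, because the list also covers voluntary withdrawal, loss to follow-up and death. They illustrate the mechanism and do not estimate harm in this trial.

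**What to change.** Reword the drop-out criteria so that non-adherence, prohibited TCM, serious adverse reactions and eligibility breaches stop study drug where needed but do not end follow-up. Keep the T30d, T60d and T90d assessments, including the T90d US7, for every randomised patient who has not withdrawn consent. Record the date of and reason for stopping drug. Analyse patients as assigned, and impute only values that are truly unobserved. A sensitivity analysis for data not missing at random would be a sensible addition to the analysis plan, but the change does not depend on it.

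The cost is a change of protocol wording and a few off-drug visits on the existing three-month schedule; the sample size is unaffected. The trade-off is that the all-randomised estimate will be somewhat diluted compared with an on-treatment one, which can still be reported alongside it.
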